### Statistical methods

Data analyses will be performed using SPSS v.25. Descriptive statistics will be generated for all relevant primary and secondary outcomes at all time-points. Multiple regression analyses will be used to identify predictors of MCI at discharge and at 12-months post-injury for the total sample and for all subgroup analyses. Latent class mixture modelling will be used to determine trajectories for different domains of cognitive functioning, as well as for selected secondary measures like anxiety, depressive mood and quality of life. Repeated measures linear mixed model analyses will be used to determine differences between the cognitive impairment versus no cognitive impairment groups for secondary outcomes. All analyses will be adjusted for factors suspected to confound results, such as level and completeness of injury, age, and education.

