**Methods:**

An inception cohort longitudinal study will assess approximately 100 individuals aged 17–80 years with acute SCI, with measures taken at three timepoints (baseline, 3 months post-baseline, and 12 months post-injury). Data relevant to medical care received within the first 24–48 h of presentation to the emergency department will be analysed, as will measures of cognition, injury characteristics, medical history, personal factors, psychological status, psychosocial functioning, and quality of life. Latent class mixture modelling will determine trajectories for the primary outcome of interest, cognitive functioning and its subtypes, and secondary outcomes of interest such as depression. Multiple regression analyses will identify predictors of MCI and its subtypes.

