### Bias

Several processes will help to reduce bias in the analyses. First, only adults with a new SCI will be recruited into the study. Second, inclusion and exclusion criteria will be strictly adhered to reduce unwanted confounding of data. Third, medical information such as PTA testing undertaken in the first 24 to 48 h after the SCI that informs the presence of mild TBI, as well as other relevant measures and TBI proxies, will be harvested from medical records to confirm the presence of a mild TBI, permitting the differentiation of TBI from other predictors of MCI. Fourth, to minimize loss to follow-up, multiple options for assessment will be provided, including online assessment, face-to face paper assessment, teleconference, and telephone assessment. Follow-up reminders by email or telephone texts will be incorporated to enhance adherence to study participation. Fifth, the use of linear mixed model repeated measures will reduce the impact of loss of missing data.

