### Study size

Our preliminary study of 150 adults with SCI [14] found a 10-point difference in the NUCOzG total mean scores (with a SD of 6.3) between the participants with MCI (*n* = 60) versus those without (*n* = 90). Therefore, the resultant effect size was large being > 1.5. For this prospective study, to test the primary outcome of interest, we are conservatively assuming a between-groups moderate Cohen’s d effect size of 0.7, a group allocation of 0.6:1 MCI: non-MCI, an alpha of 0.05, 80% statistical power, three assessment points, a compound symmetry correlation matrix (rho = 0.5), and attrition rates of 20 and 30% between assessment points. The estimated required overall sample size is at least 90 participants. This calculation was based on linear mixed model of repeated measures with a general correlation structure and the estimated sample size includes limited interaction effects [99].

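### The mixed model credited with handling missing data, and used to size the study, is not the model planned for the predictors of MCI

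*Protocol article*

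**What the plan says.** Three sections of the protocol article bear on this point.

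- **Bias.** The fifth safeguard is that "the use of linear mixed model repeated measures will reduce the impact of loss of missing data".
- **Study size.** The calculation is presented as a test of the primary outcome and rests on a repeated-measures linear mixed model. The effect to be detected is described as a "between-groups moderate Cohen’s d effect size of 0.7". The mix of participants is put at "a group allocation of 0.6:1 MCI: non-MCI". The error rates and visits are listed as "an alpha of 0.05, 80% statistical power, three assessment points". Correlation between visits is set at 0.5 with compound symmetry, and dropout is given as "attrition rates of 20 and 30% between assessment points". The result is at least 90 participants.
- **Statistical methods.** The mixed model appears once: "Repeated measures linear mixed model analyses will be used to determine differences between the cognitive impairment versus no cognitive impairment groups for secondary outcomes". Predictors of MCI are handled differently, by multiple regressions to "identify predictors of MCI at discharge and at 12-months post-injury for the total sample and for all subgroup analyses". The abstract extends this: "Multiple regression analyses will identify predictors of MCI and its subtypes". Latent class mixture modelling is planned for trajectories of the cognitive domains and of selected secondary measures.

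Identifying predictors of MCI is the second of the three primary objectives. Table 1 schedules the NUCOG at V1, V2 and V3.

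**The concern.** A mixed model helps with dropout because a participant seen at V1 but not at 12 months still contributes to the 12-month estimate through the correlation between visits. A regression fitted to one visit does not do this unless missing values are handled separately. The article claims the benefit in one section, relies on it for the sample size in another, and then assigns the model to a different set of outcomes.

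At stake is a primary objective. The Discussion intends the findings to feed rehabilitation guidelines, and the predictor results would be read as if they had the power and the robustness to dropout that the Bias and Study size sections describe.

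**Working it through.** **1. Inputs.** All are from Study size: d = 0.7; allocation 0.6:1, so the MCI share is 0.6/1.6 = 37.5%; alpha 0.05 (two-sided assumed, since the sidedness is not stated); power 80%; three assessments; rho = 0.5; attrition 20% and 30%. The abstract gives a target of about 100. Dropout is assumed monotone.

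**2. Two readings of attrition.**
- Cumulative: retention 1 / 0.80 / 0.70, so 30% are lost by 12 months.
- Per interval, as the words literally say: 0.80 × 0.70 = 0.56, so 44% are lost.

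**3. Reproducing the planned 90.** With no dropout, a two-group comparison at one visit needs

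N = (1 + 1/0.6)(1 + 0.6) × ((1.960 + 0.842)/0.7)² = 68.3, or 43 + 26 = 69 in whole people.

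For a mixed model with a separate mean at each visit, dropout multiplies N by the variance factor of the last-visit mean. With rho = 0.5 this factor is

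(2/3)/r₃ + (1/9)(1 + 2 × 0.5 + 0.75/r₂ + 0.25),

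where r₂ and r₃ are retention at V2 and V3. At r₂ = 0.80 the second term is 3.1875/9 = 0.354.

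| Reading | r₃ | Factor | N = 68.34 × factor |
|---|---|---|---|
| Cumulative | 0.70 | 0.952 + 0.354 = 1.307 | 89.3 (90) |
| Per interval | 0.56 | 1.190 + 0.354 = 1.545 | 105.6 (106) |

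The cumulative reading reproduces the stated 90. The literal reading does not.

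**4. The same comparison at 12 months on observed cases only.** Required N is 69/0.70 = 99 or 69/0.56 = 124, against 90. Power is approximately Φ(0.7 × √(n × 0.375 × 0.625) − 1.96), where n is the number seen. The t-based figure is slightly lower.

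| Enrolled | Loss | Seen at 12 months | Power, normal | Power, t | MCI cases |
|---|---|---|---|---|---|
| 90 | 30% | 63 | 76.7% | 75.4% | about 24 |
| 90 | 44% | 50 | 67.2% | 65.5% | about 19 |
| 100 | 30% | 70 | 80.9% | 79.8% | about 26 |
| 100 | 44% | 56 | 71.8% | 70.2% | 21 |

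At discharge, with 20% lost, 72 of 90 remain and power is 82.0% (normal). The shortfall is therefore at 12 months.

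**5. What the mixed model would recover.** Putting the factors from step 3 into the same normal formula, the mixed model with 90 enrolled has 80.3% power (30% lost) or 73.5% (44% lost), against 76.7% and 67.2% on observed cases.

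**6. Cases for the subtypes.** With 100 enrolled, 26 or 21 cases spread over four subtypes average 26/4 = 6.5 or 21/4 = 5.3 each.

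**The case against.** **Cognition is also analysed longitudinally.** Latent class mixture modelling of the cognitive domains is normally fitted by likelihood and can use incomplete records. This stands: it would be wrong to say that the primary outcome has no longitudinal analysis. It does not reach the visit-specific predictor regressions, which are planned separately.

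**The missing-data method may sit in an analysis plan that is not shown.** This also stands. A reader might infer complete-case deletion, but the article neither says so nor rules out imputation. The finding is the mismatch between sections, and the observed-case figures show what is at risk if nothing else is done.

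**Some stronger readings go beyond the text.**
- A reader might conclude that 44% will be lost. The stated 90 points to 30%, so 44% is the upper reading.
- A reader might take multiple regression to mean ordinary linear regression of a binary diagnosis. No link function is given, and a logistic or multinomial form fits the wording.
- A reader might divide the MCI cases by every starred entry in Table 1. Nothing says that all of them enter one model, and the named adjusters overlap with starred rows.
- A reader might conclude that the predictor effects are biased. The article gives no differential retention. If retention depended only on MCI status, the observed MCI rate would shift, but logistic odds ratios would remain consistent. If dropout depended on unobserved 12-month cognition, a mixed model would not be fully protected either.
- A reader might quote an efficiency loss from dichotomising a normal score. MCI is defined by two or more low tests within a domain, not by a cut of the NUCOG total, so such a figure would not apply directly.

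**Modelling the diagnosis is a legitimate choice.** The objectives ask for predictors of MCI and the abstract adds its subtypes. Replacing MCI with a score would change the question, so the fix should keep both.

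**Conclusion.** The inconsistency is established on the text alone. The model named as the missing-data protection, and used to size the study for the primary outcome, is assigned only to secondary outcomes, while a primary objective is answered by regressions at two separate visits. Neither the protection nor the 80% power can be claimed for those regressions as written.

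The size is moderate and depends on the attrition reading. With 90 enrolled, 12-month power on observed cases is about 75–77% (30% lost) or 65–67% (44% lost). Enrolling 100 brings it to about 80% under the first reading but only 70–72% under the second. These figures assume two-sided alpha, monotone dropout, observed cases only, and d = 0.7 for a two-group contrast carried over from Study size. That contrast stands in for a predictor effect, for which the article gives no size. The 26 or 21 remaining MCI cases limit how many predictors can be examined and leave little for subtype or subgroup regressions.

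The attrition wording is a second, linked inconsistency: read literally, it does not yield the stated 90.

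**What to change.** In Statistical methods:

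1. Analyse predictors with repeated-measures models that use all V1–V3 NUCOG data from everyone with at least one assessment. Fit a linear mixed model to NUCOG scores with visit, predictor and predictor-by-visit terms, and take the discharge and 12-month effects from it.
2. Beside it, fit a logistic mixed model for MCI, or a multiply imputed logistic regression, so that the stated aim is kept.
3. Name a short predictor list in advance, matched to the 21–26 MCI cases expected at 12 months with 100 enrolled.
4. Label the subtype and subgroup regressions exploratory.
5. Keep the latent class analysis for trajectories as planned.

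In Study size, state whether 20% and 30% are cumulative or per interval, and restate the sample size or power to match. In Bias, say which analyses the mixed-model safeguard covers.

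The cost is a few sentences and some added analysis work, with no new data collection because the NUCOG is already scheduled at all three visits. The downside is that a NUCOG-scale effect is reported next to the MCI odds ratio, and readers must be told how the two relate. The mixed model also relies on dropout being explained by the observed data.

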### Variables

Table 1 shows predictors, primary and secondary outcome measures, and the assessment timepoints relating to each measure. As the table indicates, predictors are marked by a single asterisk whereas secondary outcomes are marked by a double asterisk. *Acute monitoring* (V0) refers to the time from first presentation to the emergency department to the time of consent; at which point, routinely collected data will be retrospectively retrieved from medical records. *At rehabilitation* (V1) may vary between five and 12 weeks following SCI as participants will vary with respect to the amount of time required spent in acute care prior to proceeding to rehabilitation. *Discharge* (V2) refers to a three- to four-month period following assessments completed at V1. The timepoint *in community* refers to 12-months after the date of the initial SCI.

**Table 1 Tab1:** Predictors, primary and secondary outcome measures, and assessment timepoints

Assessment time-points	Visit-type				
Study phase	Acute monitoring	At rehab		At discharge	In community
Visit number		(V0)	(V1)	(V2)	(V3)
Eligibility pre-screening (by treating Clinician)		✓			
Informed Consent			✓		

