**Predictors* and secondary outcomes****					
**Measure**	**Measurement tool**				
Autonomic assessment*	HRV		✓	✓	✓
Current medications*	Medical records	✓	✓	✓	✓
Diagnostic evidence of TBI*	Cerebral CT/MRI scan	✓			
	GCS	✓			
	PTA	✓			
Demographics*	Medical records	✓			
Environmental factors*	Carer/family status		✓	✓	✓
	Compensation status		✓	✓	✓
Injury characteristics*	Medical records	✓			
Medical History*	Medical records	✓			
Other co-morbidities	Medical records*	✓			
	SCI SCS**		✓	✓	✓
Participation measure**	WHODAS domain				✓
Personal factors**	ADAPSS		✓	✓	✓
	Brief COPE		✓	✓	✓
	CD-RISC Short Form		✓	✓	✓
	MSES		✓	✓	✓
	WHO ASSIST		✓	✓	✓
Psychological measures**	GAD-7		✓	✓	✓
	PCL-5		✓	✓	✓
	PHQ-9		✓	✓	✓
Psychosocial measures**	Berlin Questionnaire		✓	✓	✓
	FSS		✓	✓	✓
	ISCoS pain dataset		✓	✓	✓
	PCS		✓	✓	✓
	PSQA		✓	✓	✓
	SSQ		✓	✓	✓
QoL measure**	EQ-5D-5L		✓	✓	✓
Return to work**	Questionnaire				✓
Severity of injury*	SCI: AIS and FIM	✓			
	TBI: WPTAS	✓			
Transition ED*	ED record	✓			
Vital signs*	BP, HR, RR, and Temp	✓	✓	✓	✓

*Abbreviations*: *ADAPSS* Appraisal of DisAbility Primary and Secondary Scale, *AIS* American Spinal Injury Association Impairment Scale, *BP* blood pressure, *Brief COPE* Coping Orientation to Problems Experienced, *CD-RISC* Connor-Davidson Resilience Scale, *ED* Emergency Department, *EQ-5D-5L* Euro Quality of Life 5-Dimensional 5-level, *FIM* Functional Impairment Scale, *FSS* Fatigue Severity Scale, *GAD-7* Generalized Anxiety Disorder 7-Item Scale, *GCS* Glasgow Coma Scale, *HR* heart rate, *HRV* heart rate variability, *ISCoS* International Spinal Cord Society, *MH* Mental health, *MSES* Moorong Self-efficacy Scale, *NUCOG* Neuropsychiatry Unit Cognitive Assessment Tool, *PCS* Pain Catastrophizing Scale, *PHQ-9* Patient Health Questionnaire-9, *PSQA* Pittsburgh Sleep Quality Assessment, *PTA* post-traumatic amnesia, *PCL-5* Post-traumatic Stress Disorder Checklist for the Diagnostic and Statistical Manual of Mental Disorders Firth Version, *RR* respiratory rate, *SCI* spinal cord injury, *SCI SCS* Spinal Cord Injury Secondary Condition Scale, *SSQ* Social Support Questionnaire, *TBI* traumatic brain injury, *Temp* temperature, *WHO ASSIST* World Health Organisation Alcohol Smoking and Substance Involvement Screening Test, *WHODAS* World Health Organisation Disability Assessment Scale, *WPTAS* Westmead Post Traumatic Amnesia Scale

*Predictor measure

**Outcome measure

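### WHODAS participation and return to work are measured only at V3, so the repeated-measures mixed model planned for secondary outcomes, and its stated protection against missing data, do not apply to them

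*Protocol article*

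**What the plan says.** The Statistical methods section of the protocol article names one analysis for comparing the impaired and unimpaired groups on secondary outcomes, without exception: "Repeated measures linear mixed model analyses will be used to determine differences between the cognitive impairment versus no cognitive impairment groups for secondary outcomes".

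The Bias section gives this model as the fifth protection: "Fifth, the use of linear mixed model repeated measures will reduce the impact of loss of missing data". No other analytic method for missing data is named. The fourth protection (several modes of assessment, and reminders) aims to prevent loss.

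The Variables section explains the marking in Table 1: "predictors are marked by a single asterisk whereas secondary outcomes are marked by a double asterisk". Two rows with a double asterisk, "Participation measure" (tool: "WHODAS domain") and "Return to work" (tool: a questionnaire, not described further), have a single tick, in the V3 column. All other rows with a double asterisk are ticked at V1, V2 and V3.

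The Study size section assumes "attrition rates of 20 and 30% between assessment points".

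**The concern.** A repeated-measures mixed model helps with dropout because someone who leaves before the last visit still contributes earlier values of the same outcome. The within-person correlation then carries that information to the missing visit. For WHODAS participation and return to work there are no earlier values.

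The method assigned to these outcomes therefore cannot run as a repeated-measures analysis. The natural fallback, a regression at V3, uses completers only. If people who function worse early on are more likely to be lost, and more so in one group, the comparison of those with and without MCI would be distorted. The Bias section would meanwhile lead a reader to think that the model had reduced the problem.

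**Working it through.** **1. Schedule against method.** The extracted table is broken, but the tick positions are clear. The NUCOG row has one empty visit cell and then three ticks (V1, V2, V3). The participation and return-to-work rows have three empty visit cells and then one tick (V3).

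**2. What the model becomes.** For person *i* at visit *j*, write y_ij = x_ij'β + b_i + e_ij. With only *j* = V3, the variance of y is σ_b² + σ_e². The two parts cannot be separated and no correlation can be estimated. The likelihood is that of an ordinary linear regression, and a person without a V3 value adds no term to it.

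**3. The plan's own N.** Inputs from Study size: d = 0.7, ratio 0.6:1, alpha 0.05 (two-sided assumed), 80% power, three visits, compound symmetry with rho = 0.5. For a contrast at the last visit,

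N = 1.6 × (1 + 1/0.6) × ((1.960 + 0.842)/0.7)² × v = 68.34 × v,

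where v is the variance of the V3 mean relative to complete data, obtained by generalised least squares with monotone dropout.

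| Reading of 20% and 30% | Retained at V1, V2, V3 | v, three-visit model | N |
|---|---|---|---|
| Cumulative | 1, 0.8, 0.7 | 1.3065 | 89.3, so 90 |
| Sequential | 1, 0.8, 0.56 | 1.5446 | 105.6 |

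The stated 90 is reproduced under the cumulative reading. That figure counts on the earlier visits of people who drop out.

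**4. Observed at V3.** Cumulative: 0.7 × 90 = 63. Sequential: 0.8 × 0.7 × 90 = 50.4, about 50.

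**5. Precision of a V3-only outcome.** Completers alone give v = 1/0.7 = 1.4286 or 1/0.56 = 1.7857. The variance is larger than under the three-visit model by 1.4286/1.3065 = 1.09 or 1.7857/1.5446 = 1.16. At N = 90 the groups are 56.25 and 33.75, and SE = √(v × (1/56.25 + 1/33.75)). The documents give no effect size for these outcomes, so d = 0.7 is borrowed.

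| Reading | Power, three-visit model | Power, V3 only |
|---|---|---|
| Cumulative | 80.3% | 76.7% |
| Sequential | 73.5% | 67.2% |

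**6. Possible bias (illustration).** Assumptions: true difference 0.70 SD; correlation 0.5 to 0.7 between earlier functioning and the V3 outcome; logistic retention on earlier functioning, calibrated to the overall retention. The slopes for non-MCI and MCI were (0.5, 0.5) and (1, 1) for a common mechanism, and (0.3, 1) and (0, 1) for a differential one. Completer differences, in SD (a repeat run agreed to about 0.01):

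| Retained | Same mechanism in both groups | Stronger dependence in MCI |
|---|---|---|
| 56% | 0.61 to 0.68 | 0.38 to 0.53 |
| 70% | 0.63 to 0.68 | 0.46 to 0.56 |

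In the repeat run, a regression estimate that also used the earlier value recovered 0.70 in every scenario. This is the information that imputation or weighting would draw on.

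**The case against.** A condensed article gives each family of analyses one sentence, and the model for a single-visit outcome would normally be set out in a full analysis plan. That is fair as to the details of imputation, but the point does not rest on missing detail. The article assigns a method to all secondary outcomes and credits it with protection against missing data, and its own table rules both out for two of them.

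It can also be said that analysts will simply fit a V3 regression. They can, but this is the completers-only analysis described above. Statistical methods adjusts all analyses for confounders such as level and completeness of injury, age and education, so dropout explained by these is partly addressed. Earlier cognition, mood and functioning are not clearly among them. The retention measures in the Bias section do apply to V3 outcomes, but they do not help once a person is lost.

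The objections to size carry more weight:

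- The 56% is only one reading of the attrition figures, and the 70% reading fits the plan's own N better.
- With the same dropout mechanism in both groups the bias is small, at most about 0.09 SD (0.70 − 0.61).
- The larger values need a differential mechanism that nothing in the document establishes.

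A reader might also infer that the plan claims missing data are fully handled. The Bias section claims only a reduced impact. Nor does the document support saying that these two outcomes carry a conclusion about community reintegration: the Secondary objectives section gives depression, health complications and quality of life as its examples, and the measures of these are all repeated at V1 to V3.

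**Conclusion.** The point stands for two secondary outcomes. The mixed-model sentence and the missing-data sentence cannot both be true of outcomes measured once. As written, WHODAS participation and return to work would be compared in completers only: 63 of 90 or about 50 of 90, depending on how the attrition is read.

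The conflict rests on the text and Table 1 alone. The size of any bias does not: about 0.61 to 0.68 SD instead of 0.70 under a common dropout mechanism, and about 0.38 to 0.56 SD under a differential one, are illustrations on assumed inputs and not predictions.

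Three stronger readings are not supported:

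- The stated N = 90 is not shown to be wrong. It concerns the primary outcome, and both are unaffected.
- The other secondary outcomes are not at fault, since each is measured three times.
- No figure can be put on distortion of the return-to-work rate. The document gives neither a base rate nor the scale, and yes/no coding is an assumption.

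The weight is modest, but the repair is cheap and worth making.

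**What to change.** Limit the mixed-model sentence in Statistical methods and the fifth item in Bias to outcomes measured at V1, V2 and V3.

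For the two V3-only outcomes, name a regression suited to the scale: linear for WHODAS participation, and logistic for return to work if it is recorded as yes/no. Pair it with multiple imputation or inverse-probability-of-retention weighting that uses V1 and V2 data, such as NUCOG, PHQ-9, EQ-5D-5L, MSES and SCI SCS, together with the injury covariates. Both methods assume that loss is explained by the variables used, and the text should say so.

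The cost is a few sentences and a little more analysis work on data already scheduled. Confidence intervals may be slightly wider. No extra visit or participant is needed.

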### Participant allocation to groups

Allocation to groups will be based on the absence or presence of cognitive impairment as presented in Fig. 1. Cognitive performance will be assessed using a validated neuropsychological screen. The number of participants will be up to 50 per group, and recruitment will be stratified so that similar numbers of females/males and tetraplegia/paraplegia are allocated to groups. The criteria for a diagnosis of MCI, and hence allocation to cognitively impaired versus not-cognitively impaired groups, will accord with those proposed by Jak et al. [77], requiring scores > 1 standard deviation below normal on ≥2 tests within a cognitive domain on a standardised neuropsychological test. These criteria have been selected as they have demonstrated greater stability over time when compared to alternative conventional criteria as proposed by Petersen, that require scores of > 1.5 standard deviations below normal on a single test within one cognitive domain on neuropsychological testing. We will subtype MCI as follows: *Single Domain Amnestic* if only the memory domain is impaired; *Single Domain Non-Amnestic* if only one non-memory domain is impaired; *Multiple Domain Amnestic* if memory and at least one other domain shows impairment; and *Multiple Domain Non-Amnestic* if there are impairments in more than one non-memory domain [78].

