## Discussion

Cognitive impairment is a multifaceted condition yet there is no research into its subtypes in people with an acute SCI. Different operationalizations of cognitive impairment pervade the SCI literature making it difficult to specify the extent and nature of the problem. Factors proposed to account for cognitive impairment in individuals with SCI include age at injury, autonomic dysfunction, cerebrovascular compromise, hypertension, hypotension, and psychosocial factors like depressive mood, chronic pain, and fatigue. It is possible that in some cases cognitive impairment can be associated with an iatrogenic consequence of medication-use, however, research into this hypothesis involving patients with SCI is sparse. Research is needed to identify all predictors of cognitive impairment following SCI, with specific attention given to subtyping. Studies that incorporate longitudinal designs and repeated measures permitting the identification of distinct trajectories and predictors of MCI are required. Therefore, this study will incorporate predictor and outcome measures in a prospective design beginning in the first 24-h of admission to the emergency department following SCI, the timeframe in which assessments of mild TBI must be made.

TBI is a common comorbidity of SCI that is assumed to be a significant contributor to cognitive impairment, and this must be carefully accounted for when investigating the unique contribution of other possible contributors to cognitive impairment. Various biopsychosocial measures (e.g., heart rate, mood, fatigue, and anxiety) will be included in the study, permitting the investigation of the additive and/or multiplicative risks that contribute to MCI. We propose the findings of this study will for the first time reveal important differences in the manifestation of cognitive impairment in individuals with SCI, and seek to develop evidence-based guidelines that will incorporate study findings to guide the rehabilitation of individuals with SCI who concurrently have MCI.

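### With about 19–30 expected MCI cases, the regression meant to identify predictors of MCI supports only a few terms; the plan should name a penalised method and limit what enters each model

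*Protocol article*

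**What the plan says.** The second primary objective is to identify predictors of MCI, with mood disturbance, polypharmacy and TBI as examples, and moderators such as education, premorbid intelligence and practice effects. The abstract gives the method: "Multiple regression analyses will identify predictors of MCI and its subtypes". The Statistical methods section applies it at discharge and at 12 months after injury, in the total sample and in subgroups, using SPSS v.25, and adds: "All analyses will be adjusted for factors suspected to confound results, such as level and completeness of injury, age, and education". MCI is a yes/no classification under Participant allocation to groups.

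The aims are multivariable. The abstract faults earlier work for not handling several predictors and their interactions, and the Discussion describes the chosen measures as "permitting the investigation of the additive and/or multiplicative risks that contribute to MCI".

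The Study size section supports a different analysis, a mixed-model comparison of the MCI and non-MCI groups. It assumes "a group allocation of 0.6:1 MCI: non-MCI" and concludes: "The estimated required overall sample size is at least 90 participants". The abstract plans for about 100 people, and the allocation section says "The number of participants will be up to 50 per group".

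**The concern.** For a binary outcome, the smaller outcome group limits how many coefficients a model can carry. When cases per coefficient are few, maximum-likelihood logistic regression pushes odds ratios away from 1, and the model appears to discriminate in the data it was fitted to even when nothing predicts the outcome. No sample-size argument in the article covers this objective, and nothing stated limits the number of terms.

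The results are meant to separate the effect of TBI from other factors and to inform rehabilitation guidelines. An overstated TBI effect, or a risk profile that does not replicate, would carry into that use.

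**Working it through.** **1. The plan's own figure.** Inputs from Study size: d = 0.7, ratio 0.6:1, alpha 0.05 (two-sided assumed), power 80%, three assessments, compound symmetry with rho 0.5, attrition of 20 and 30%.
- Single time point: non-MCI n = (1 + 1/0.6) × (1.960 + 0.842)² / 0.7² = 42.7. The total is 42.7 × 1.6 = 68.3.
- Mixed model, group difference at the last visit, retention 100/80/70%: 89.3, so 90. This reproduces the stated figure.
- With the losses compounded (100/80/56%) the same calculation gives 105.6. The 90 therefore fits a reading in which 30% is the cumulative loss.

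This confirms that the 90 answers the group comparison. It says nothing about the predictor regression.

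**2. Expected MCI cases.** MCI share = 0.6/1.6 = 0.375, assumed unchanged over time. Cases = N × retention × 0.375.

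| N | Discharge (80%) | 12 months (70%) | 12 months (56%) |
|---|---|---|---|
| 90 | 27.0 | 23.6 | 18.9 |
| 100 | 30.0 | 26.2 | 21.0 |

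The most favourable reading, 50 per group, gives 50 × 0.8 = 40 at discharge and 50 × 0.56 = 28 to 50 × 0.70 = 35 at 12 months.

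**3. How many terms.** Counting one coefficient per factor:
- Four named adjusters plus one predictor: 5.
- Four adjusters plus the three example predictors: 7. Adding premorbid intelligence and practice effects (education is already an adjuster): 9. Adding one product term for each of the three example moderators: 12.

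The article does not specify a 9–12 term model, but its stated examples lead to one.

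**4. Cases per term**, from 18.9 to 30 cases: 3.8–6.0 with 5 terms, 2.1–3.3 with 9, and 1.6–2.5 with 12.

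**5. Simulation.** Logistic models with independent predictors, one having a true odds ratio of 2.5, and 50 to 80 analysed patients (19 to 30 cases). The null AUC is the apparent value when no predictor matters (truth 0.50).

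| Terms | Median estimated OR, maximum likelihood | Null apparent AUC |
|---|---|---|
| 5 | about 2.7–2.8 | about 0.64–0.68 |
| 9–12 | about 2.9–3.8 | about 0.69–0.79 |

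Firth-penalised fits of the same models return about 2.4–2.6.

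A separate simulation with a true odds ratio of 2 per SD agrees. Five terms give 2.13–2.27 at 19 to 27 cases, and eight terms give 2.34 at 24 cases. At 40 cases of 80, five terms still give 2.14 with a null AUC of 0.64, so the most favourable recruitment reduces the problem without removing it.

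**The case against.** The strongest reply is that the article does not describe the model criticised here. It does not say logistic, maximum likelihood, odds ratios, AUC or simultaneous entry, and a condensed article may leave link function, selection and shrinkage to an analysis plan that is not shown. This stands to the extent that the logistic reading is an inference from a yes/no outcome, and that penalisation is neither stated nor ruled out. It does not dispose of the point. The article itself fixes a named method, an open-ended adjustment set and multivariable aims for a primary objective, beside a sample size derived for another question.

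Three stronger readings are tempting and are not supported:

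- **That all the measures marked as predictors in Table 1, 19 when cells are split, plus four adjusters form one 23-term model.** No section says so. Table 1 has 11 predictor rows. Level, completeness and age overlap with the injury, AIS and demographic entries. The TBI screening section draws GCS, imaging and post-traumatic amnesia into one determination of TBI. Larger models would be worse, but their figures do not measure this plan.
- **That 19–27 cases is a settled range.** It applies at the minimum N. The 19 uses compounded attrition, whereas the stated 90 reproduces only with 30% cumulative loss. The Background reports that MCI may remit, persist or worsen, so the later share could differ from 37.5%.
- **That frequent chance findings show sparse-data bias.** With 12 null terms, the chance of at least one p < 0.05 is already 1 − 0.95^12 = 46% at any sample size, against 51–54% simulated. That is mostly multiplicity, which penalisation does not cure.

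It is also fair to say that the gain from Firth is small in a five-term model.

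**Conclusion.** The concern holds in a limited form. At the plan's own figures, about 27–30 MCI cases at discharge and 19–26 at 12 months can support only a few coefficients. For four adjusters plus one predictor, a true odds ratio of 2.5 is overstated by roughly 8–12% (2.7/2.5 to 2.8/2.5). At 9–12 terms, which the stated aims make plausible, the overstatement is roughly 16–52% (2.9/2.5 to 3.8/2.5), and a model of pure noise shows an AUC of about 0.69–0.79.

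This rests on four assumptions: a logistic model fitted by maximum likelihood, a constant 37.5% MCI share, the stated attrition, and independent predictors with one coefficient each. Correlated or categorical predictors would change the figures. The article should be amended because a better method is available at little cost. The evidence does not show that the planned analysis must fail.

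**What to change.** In Statistical methods:

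1. Name Firth-penalised logistic regression, with profile penalised-likelihood intervals, for the MCI predictor models.
2. Combine the TBI indicators into the single determination described under TBI screening, and enter that one variable.
3. Estimate each predictor adjusted for the named factors plus TBI. TBI must be included because the Discussion requires it to be accounted for when other contributors are assessed. With one coefficient per factor this is six terms, or 18.9/6 = 3.2 to 30/6 = 5.0 cases per term.
4. Fit any multi-predictor, interaction or risk-profile model with penalisation. Report the bootstrap optimism-corrected AUC beside the apparent one, and label the model exploratory.

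The cost is analysis wording and a package or extension outside base SPSS. Recruitment, visits and measures do not change. The downside is that effects and discrimination will look less favourable. Multiplicity across many tested predictors is a separate issue that these changes do not solve.
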